**Research Protocol. Version 1.**

**October 2003**

# MEDITERRANEAN DIET IN PRIMARY CARDIOVASCULAR PREVENTION

## Research Plan

### A. SPECIFIC AIMS

A Mediterranean-type diet (MeDiet) has been widely considered as a model of healthy eating. The adherence to a MeDiet was associated with lower coronary mortality in a cohort study (Trichopoulou, 2003) and in a relatively small trial with patients after a myocardial infarction (De Lorgeril, 1999), but no large primary prevention trial with clinical events as end-point has been performed. Furthermore, there are discrepancies among nutrition experts because of the high-fat content of MeDiets (up to >40% of total energy intake), which is in conflict with the usual recommendation to follow a low-fat diet in order to avoid overweight/obesity and to prevent coronary heart disease (CHD) (Ferro-Luzzi, 2003; Jequier, 2002; USDA, 2000; Connor, 1997; Bray, 1998). The potential cardiovascular preventive effect of MeDiets in the face of the huge and increasing global burden of cardiovascular disease (Reddy, 2004; WHO, 2003a) makes the answer to this question a priority for public health. Other important reasons to thoroughly assess the effect of dietary guidelines based on the MeDiet, include: a) the long tradition of following MeDiets without any harm in Southern Europe, where life expectancy is extraordinarily high (Willett, 1995), b) the low incidence of CHD in these countries in spite of having similar or even higher levels of classical risk factors compared to the US population (Tunstall-Pedoe, 1999); c) the diversity of mechanistic and epidemiological observations of beneficial effects on cardiovascular health of the consumption of key components of the MeDiet, such as monounsaturated fatty acids (MUFA), extra-virgin olive oil (EVOO), or nuts; and d) the higher palatability, acceptance and compliance with MeDiets in comparison with low-fat diets (McManus, 2001).

In the era of evidence-based medicine, nutritional recommendations should be based in large scale randomized intervention studies in which clinically relevant (“hard”) end-points are evaluated. However, no randomized controlled trial has ever been conducted to assess to what extent a MeDiet offers greater benefits than a usual diet in the primary prevention of cardiovascular events. This is the research plan of the first primary prevention trial, the PREDIMED Study (PREDIMED meaning ***PRE**vencción con **D**ieta **MEDiterránea***), which plan to test the effects of a MeDiet intervention on prevention of cardiovascular disease. The results of this large scale randomized trial should provide the strong evidence required to support dietary guidelines for the general public. This study needs to be conducted in Spain for two reasons: a) It is more cost-effective to expand an ongoing trial that has developed all its infra-structure than to start a new one; b) the US population is not yet prepared to adopt a MeDiet in a short period of time.

#### A.1. Primary Specific Aims

Specific Aim 1 (**MeDiet+Olive oil**): to test the effect of a MeDiet enriched with supplemental extra-virgin olive oil on a composite endpoint of cardiovascular death, myocardial infarction, and stroke.

Specific Aim 2 (**MeDiet+Nuts**): to test the effect of a MeDiet enriched with supplemental walnuts, almonds, and hazelnuts on a composite endpoint of cardiovascular death, myocardial infarction, and stroke

## **A.2. Other Specific Aims**

We will ascertain changes in blood lipids, blood pressure (BP), markers of inflammation and other intermediate markers of cardiovascular risk to better understand how dietary changes are able to modify the risk of clinical events.

## **B. BACKGROUND AND SIGNIFICANCE**

Cardiovascular disease is the main cause of death worldwide at the turn of the XXI century. Western countries, including the US, currently continue to exhibit unacceptable high absolute rates of cardiovascular morbidity and mortality. Furthermore, these diseases constitute emerging and neglected epidemics in developing countries (**WHO, 2003a, WHO, 2003b**). Surprisingly, a low incidence of CHD is found in some developed countries such as France, Spain, Greece, Italy, and Portugal, leading to a higher life expectancy as compared with Northern European countries or the US (**WHO, 1993; Tunstall-Pedoe, 1999**). The Mediterranean food pattern has been the factor most frequently invoked to explain this health advantage.

### **B.1. The Mediterranean diet (MeDiet)**

The MeDiet is identified as the traditional dietary pattern found in olive-growing areas of Crete, Greece and Southern Italy in the late 1950s and early 1960s. Its major characteristics are: a) a high consumption of non-refined grains, legumes, nuts, fruits and vegetables; b) a relatively high-fat consumption (even greater than 40 percent of total energy intake) mostly from MUFA, which accounts for 20 percent or more of the total energy intake; c) olive oil used to cook and for dressing salads is the principal source of fat; d) fish consumption is moderate to high; e) poultry and dairy products (usually as yogurt or cheese) are consumed in moderate to small amounts; f) a low consumption of red meats, processed meats or meat products; g) a moderate alcohol intake, usually in the form of red wine consumed with meals (**Trichopoulou, 1995**).

Replacing saturated fat with MUFA from olive oil produces a decline in total and LDL cholesterol comparable to that attained by low fat diets, but HDL cholesterol is maintained at higher levels, thus obtaining a net advantage on the overall lipid profile (**Perez-Jimenez, 2002; Willett, 2000**). In addition, LDL particles enriched with oleic acid and with a lesser PUFA content may be less easily converted to modified, proinflammatory LDL particles. High olive oil consumption, the hallmark of MeDiet (**Hu, 2003**), is partially responsible for these effects. Additional mechanisms have been suggested for the beneficial effect of the MUFA-rich MeDiet (**Perez-Jimenez, 2002**). Among them (see below), it has been reported that incorporation of oleic acid into cultured endothelial cells decreases the expression of endothelial leukocyte adhesion molecules with reductions in VCAM-1 and inhibition of nuclear factor-kappaB activation (**Carluccio, 1999**). Postprandial factor VII is significantly lower after a MUFA-rich diet. Olive oil is also associated with a reduced DNA synthesis in human coronary smooth muscle cells (**Mata, 1997**).

The background of a long and ancient tradition with no evidence of harm makes the MeDiet very promising for public health. The high fruit and vegetable intake adds to its high antioxidant content and other mechanistic benefits provided by the polyphenols present in EVOO and red wine. Wide sectors of the scientific community and of consumers believe in a cardio-protective role for MeDiets. This hypothesis fits well into the current paradigm of studying **overall dietary patterns** instead of simply assessing isolated nutrients in

nutritional epidemiology. The rationale is that food items and nutrients may have synergistic or antagonistic effects when they are consumed in combination. Additionally, overall patterns better represent the dietary practices found in free-living populations and therefore provide more useful epidemiological information (**Jacques, 2001; Jacobs, 2003**). Consequently, they have a higher potential for acceptability, palatability and future compliance when they are recommended in behavior counseling. Therefore, in spite of its relatively high fat content, the theoretical advantages of the MeDiet are multiple. To increase vegetable consumption, the fat-free or low-fat dressings are less acceptable than the use of olive oil or other full-fat salad dressings. The sautéing or stir frying of vegetables with variable amounts of olive oil instead of using low-fat spreads or steaming increases taste and results in long-term maintenance of a vegetable-rich diet. These preparation and cooking techniques are typical of MeDiet, where the custom is to cook vegetables in olive oil to enhance flavor. Hence, in health promotion and nutritional education a better compliance with MeDiet will be expected. In fact, a recent trial of weight loss (**McManus, 2001**) reported a better adherence to a MeDiet than to a low-fat diet. Participants viewed this diet as more tasty than low-fat regimens, and this may have been the cause of their increased long-term compliance.

However, at present, there is evidence of an undesirable departure from traditional MeDiets in Southern European countries, especially among younger people (**Sanchez-Villegas, 2003; Costacou, 2003**), with increasing consumption of red meats, processed meats, and foods and beverages high in simple sugars. In addition, the traditional consumption of EVOO is being replaced by other refined vegetable oils of inferior quality. The presumable antiatherogenic properties of olive oil have been mainly attributed to its high content in MUFA oleic acid. However, in recent years converging evidence indicates that polyphenols only present in EVOO significantly contribute to these benefits. The concentration of phytochemicals in oils is influenced by the oil extraction procedures. EVOO is obtained from the first pressing of the ripe fruit and has a high content in antioxidants (tocopherols, polyphenols, flavonoids) and sterols. Lower quality olive oils (refined olive oils, ROO) lose nearly all of this antioxidant capacity because they are refined by physical and chemical procedures, they are mostly coloreless and aroma free, although their fatty acid composition is close to that of EVOO (**Ramirez-Tortosa, 1999; Lercker, 2000**). EVOO polyphenolic derivatives (hydroxytyrosol, tyrosol and their secoiridoid derivatives) have shown strong antioxidant and anti-inflammatory activity *in vitro* (**De la Puerta, 1999; 2001; Manna, 2002; Visioli, 2002**). In randomized cross-over trials that compared EVOO with ROO (in doses similar to the usual MeDiet), EVOO increased plasma antioxidant capacity and decreased serum thromboxane B2 production. It also increased LDL resistance to oxidation. EVOO affords better protection than dietary alpha-tocopherol against lipid peroxidation (**Mataix, 1998**) and shows a more comprehensive array of effects related to atherosclerosis reduction, such as reducing oxidative stress (**Visioli, 1998**). Consequently, ROOs are thought not to provide such high cardiovascular benefits as EVOO and It is important to distinguish between each type of oil when analyzing the effects of olive oil on cardiovascular risk. EVOO has been shown to induce a dramatic regression of atherosclerosis in a hamster model (**Mangiapane, 1999**). In a randomized trial including 22 hypercholesterolemic men, EVOO improved endothelial function (**Fuentes, 2001**), and in another trial with 23 hypertensive patients, it significantly reduced BP and the need for antihypertensive medications (**Ferrara, 2000**). In any case,

we assume that the effect of the overall MeDiet pattern will be more important than the isolated action of a single component.

## **B.2. Available evidence about MeDiet and cardiovascular prevention**

A MeDiet was inversely associated with mortality from all-causes in several small observational cohort studies of elderly people (**Trichopoulou, 1995; Kouris-Blazos, 1999; Lasheras, 2000**). Recent findings from the Greek EPIC cohort, with more than 22,000 participants, suggested that a higher adherence to the MeDiet is associated with a reduction in total mortality and, more specifically, in coronary mortality (**Trichopoulou, 2003**). Two recent case-control studies also found an inverse association between adherence to the MeDiet and incidence of non-fatal coronary events (**Martinez-Gonzalez, 2002; Panagiotakos, 2002**). Two secondary prevention trials found a remarkable reduction in reinfarction or death when coronary patients were assigned to a so-called "Mediterranean diet" (**De Lorgeril, 1999; Singh, 2002**). The first of these trials, the Lyon Diet Heart Study (**De Lorgeril, 1999**), found a 50%-70% relative reduction in the risk of mortality or reinfarction when patients who had suffered a myocardial infarction were assigned to an experimental diet rich in bread, vegetables, fish, and fruit and low in red meat (replaced with poultry). Butter and cream were replaced with a special margarine rich in alpha-linolenic acid (ALA). The other trial (**Singh, 2002**) found a 52% relative reduction in total cardiac endpoints with an experimental diet rich in fruits, vegetables, nuts, whole grains and mustard seed or soy bean oil. The 50% to 70% observed reduction of cardiac events in the experimental group of the Lyon trial after 46 months leads us to think that if these results were generalized to non-Mediterranean populations, substantially enhanced and efficient methods to reduce CHD would be available. It would be shortsighted not to acknowledge the vast public health benefit that a MeDiet could provide with adoption by the healthy population-at-large if the findings of the secondary trials are also confirmed in primary prevention trials. The American Heart Association (AHA) has given attention to MeDiets as potentially useful for the prevention of CHD, but a cautious recommendation has been issued highlighting that more studies are needed before advising people to follow a MeDiet. These studies will disentangle whether the diet itself or other factors (such as more physical activity, a beneficial genetic background or stronger social support systems) account for the lower incidence of CHD in the Mediterranean countries (**Kris-Etherton, 2001a**).

## **B.3. Limitations of published studies on MeDiet and cardiovascular prevention**

The two published trials using so-called "MeDiets" have included patients who had already experienced a clinical event, i.e. they were **secondary** prevention trials (**De Lorgeril, 1999; Singh, 2002**), and their results may not be extrapolated to issue dietary guidelines for primary prevention. Additionally, major aspects of the design and methods of these two trials have been overtly criticized. Both trials were designed to provide the experimental group with a high amount of ALA. However, no special consideration was given to olive oil, which is the major source of dietary fat in Mediterranean countries or to the special relevance of EVOO as an important source of polyphenols. On the other hand, no protective effect for olive oil was observed in the Greek EPIC cohort (**Trichopoulou, 2003**), thus raising the issue of whether the large amount of fat provided by olive oil is in fact affording protection against CHD (**Hu, 2003**). In the Lyon Diet Heart Study, the

assessment of the true dietary patterns and nutrient intakes at baseline and at end of the study were reported for only a subset of participants (30% of the control group and 50% of the experimental group). In addition, no biochemical verification of dietary compliance was done. Thus, the diet followed by most participants completing the trial is not known (**Kris-Etherton, 2001a; Robertson, 2001**). A third major issue was that only 12.9 percent of energy intake was provided by MUFA in the group assigned to "MeDiet" in the Lyon Trial. In the Indo-Mediterranean Study, the percentage of MUFA intake was even lower (10% of total energy) and the diet of the intervention group (26% fat) could be actually interpreted as a low-fat diet. These values for fat and MUFA intake are far below the higher MUFA content ( $\geq 20\%$ ) of the traditional MeDiet (**Perez-Jimenez, 2002**). This is contrary to what should be expected with a MeDiet intervention and these two trials have actually applied interventions not fully in line with the traditional MeDiet. Additional concerns about the Lyon trial are related to the low number of observed end-points (44/14, in the control and intervention group respectively), the improbably large reduction in relative risk (RR) (in spite of not observing changes in some of the classical risk factors), and to the fact that the trial was stopped very early (after 27 months of follow-up). **No available randomized trial has assessed an EVOO-rich MeDiet in primary cardiovascular prevention. The PREDIMED study will be the first large trial to randomize high-risk patients to follow-up a traditional MeDiet for primary cardiovascular prevention.** The PREDIMED trial is designed to overcome the previous limitations and to provide results with the best quality of evidence.

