### **B.3. Limitations of published studies on the MeDiet and cardiovascular prevention**

The only published trial using a so-called “MeDiet”, the Lyon Diet Heart Study (**De Lorgeril, 1999**), included patients who had already experienced a clinical event, i.e. it was a secondary prevention trial, and its results may not be extrapolated to primary prevention. Besides, the results of this trial, showing a 50-70% reduction in reinfarction and CHD mortality in the group assigned the MeDiet rich in alpha-linolenic acid, seem to be too good to be true, and major aspects of the design and methods have been criticized. However, no special consideration was given to olive oil, which is the major source of dietary fat in Mediterranean countries (**Martinez-Gonzalez, 2004b**). On the other hand, no clear protective effect of olive oil was observed in the Greek EPIC cohort (**Trichopoulou, 2003**), thus raising the issue of whether the large amount of fat provided by olive oil is in fact affording protection against CHD (**Hu, 2003**). In the Lyon Diet Heart Study, dietary assessments at baseline and at the end of the study were reported for only a subset of participants (30% of the control group and 50% of the experimental group). In addition, no biochemical markers of adherence were obtained. Thus, the diet followed by most participants completing the trial is not known (**Kris-Etherton, 2001a; Robertson, 2001**). A third major issue was that only 13% of energy intake was provided by MUFA in the group assigned to the so-called “MeDiet” in the Lyon trial. This value for MUFA intake is far below the  $\geq 20\%$  content of the traditional MeDiet (**Perez-Jimenez, 2002**). Additional concerns about the Lyon Diet Heart study are related to the low number of observed endpoints (44/14, in the control and intervention group respectively), the improbably large reduction in relative risk (RR) (in spite of the lack of changes in most classical risk factors), and the fact that the trial was stopped early (after 27 months of follow-up). No study has assessed a true MeDiet rich in olive oil for cardiovascular endpoints. The PREDIMED study is the first large trial to randomize high-risk patients to a traditional MeDiet and a control, low-fat diet for primary cardiovascular prevention, thus overcoming previous limitations and aiming to provide the best quality of evidence

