#### **D.4. Sample size**

A sample size of  $n=6,999$  with randomization to 3 equally sized groups (two intervention groups and one control group, 2,333 patients each) will provide sufficient statistical power to evaluate the effect of the Mediterranean food pattern on the primary outcome (fatal or non-fatal myocardial infarction and fatal or non-fatal stroke). The sample size estimates were computed by comparing two binomial proportions representing the event rates in one of the treatment groups and in the control group. We assumed an 80% power ( $1-\beta=0.8$ ) and ( $1-\alpha/2=0.975$ ) for a 2-sided p-value of 0.05. To estimate the projected cumulative incidence in the control group, we used the number of events observed in the first year follow-up (rate of 1.3%). Adapting this figure to a 6-year follow-up and taking into account the aging of our study population during follow-up, an 11% average absolute risk can be assumed for the control group. The minimum relative decrease in number of events in the intervention groups should be 25%. Then,  $p_1 = 0.11$  and  $p_2 = (0.117)(0.75) = 0.0825$ . With these assumptions, the total number of participants required is 1,877 per group. We plan to include 2,333 subjects in each group to allow for 10% losses during follow-up and also for a lower incidence than expected.

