#### D.12. Statistical Analyses

The analyses will be based on the intention-to treat principle. With the actual sample size, it is assumed that we will have enough statistical power to evaluate the effects of the MeDiet (the two MeDiet groups considered as a single one) compared to the Low-fat Control diet on the primary prevention of cardiovascular diseases. We also might be able to assess differences in outcomes for the two MeDiets if the specific supplements of EVOO and mixed nuts prove to be differentially cardioprotective. The main variable for analysis will be time from randomization to event. For a given outcome, the time of the event will be defined as the number of days from randomization to the first post-randomization diagnosis, as determined by the adjudicator. For silent MI, the date of the follow-up EKG will be applied. Participants without a diagnosis will be censored at the time of last follow-up contact. The generally accepted method for analyzing this type of data is the log rank statistic. It has the advantage of requiring no assumptions other than the random assignment of the intervention. This analysis will be the primary measure of the success or failure of the trial. However, if baseline imbalances between groups are observed for any of the main CHD risk factors, a Cox proportional hazard analysis will be conducted stratified by FC, age, sex and adjusted for major risk factors. Primary outcome comparisons will be estimated as hazard ratios. Adjustment for other relevant variables (body mass index, physical activity, education level, marital status) also will be applied.

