#### D.13.2. Data analysis

The data from the PREDIMED trial will be analyzed at 5 intervals (4 interim analyses and the final analysis). The 4 interim analyses to decide on the continuation of the PREDIMED trial will be conducted after 2, 3, 4 and 5 years of median follow-up. The 2-sided p-values for stopping the trial at each interim analysis (1st to 4th) are respectively  $5 \times 10^{-6}$ , 0.001, 0.009 and 0.02 for benefit, and  $9 \times 10^{-5}$ , 0.005, 0.02 and 0.05 for adverse effects, according to asymmetric O'Brien-Fleming boundaries (**O'Brien, 1979**). The actual recommendation regarding stopping or continuing the trial will be made by the DSMB. There are 3 potential reasons for early ending of the trial: a) efficacy of MeDiet may be demonstrated; b) harmful effects of the intervention may be discovered; c) there may be no hope for a reasonable evaluation of the proposed hypothesis (i.e., if a small intervention differential exists, power may be seriously compromised and early termination of the trial may be considered). Early termination should be considered only if the intervention effect is really great.

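### The plan allows four early stops for benefit but names no hazard ratio or interval that allows for stopping; after an early stop the ordinary hazard ratio would tend to overstate the benefit

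*Supplement*

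**What the plan says.** All sections are in the current protocol (Version 2, May 2009) unless noted.

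- **B.3** doubts an earlier secondary-prevention diet trial. Its concerns include few endpoints (44 and 14), an improbably large risk reduction, "and the fact that the trial was stopped early (after 27 months of follow-up". Version 1 (October 2003) said much the same: "and to the fact that the trial was stopped very early (after 27 months of follow-up".
- **D.13.2** plans four interim analyses and a final one. The interim looks "will be conducted after 2, 3, 4 and 5 years of median follow-up". The two-sided p-values for stopping for benefit are 5×10⁻⁶, 0.001, 0.009 and 0.02, described as asymmetric O'Brien-Fleming limits. The DSMB makes the recommendation, and early termination is reserved for a very large effect.
- **D.12** makes the log-rank test primary. On estimation it says: "Primary outcome comparisons will be estimated as hazard ratios". The adjustments it mentions are for baseline covariates.
- **D.4** gives the design inputs: "We assumed an 80% power", "for a 2-sided p-value of 0.05", "an 11% average absolute risk can be assumed for the control group", and a 25% relative reduction as the effect to detect.

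Neither D.12 nor D.13.2 says how the hazard ratio or its interval will be reported if the trial stops at an interim look. The contents page lists a statistical analysis plan, but no separate plan is in the text shown.

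**The concern.** A trial that stops because its test statistic crossed a benefit limit has been selected partly for a favourable chance deviation. The ordinary maximum-likelihood HR at that moment is, on average, further from 1 than the truth. O'Brien-Fleming limits control the type I error and do not remove this bias from the estimate. Covariate adjustment does not address it either.

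The size of the risk reduction is at stake, as is the coverage of the interval if the true effect is weaker than planned. B.3 shows that the authors regard a very large effect combined with early stopping as a reason for caution. Their own plan should therefore say how it will handle the same issue.

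**Working it through.** **1. Reproduce the plan's figures.**

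Sample size, with p₁ = 0.11 and p₂ = 0.11 × 0.75 = 0.0825 (D.4 prints 0.117 in that product, but its stated result matches 0.11). The two-proportion formula with pooled variance at two-sided 0.05 and 80% power gives n = 1,805 per group. With continuity correction, n/4 × [1 + √(1 + 4/(nΔ))]² and Δ = 0.0275, this is 1,805/4 × [1 + √(1 + 4/49.64)]² = 1,877, which is D.4's figure.

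Limits: for five equally spaced looks the O'Brien-Fleming constant is 2.04, and z = 2.04 × √(5/i) gives p = 5.1×10⁻⁶, 0.0013, 0.0085 and 0.023 for i = 1 to 4. These agree with D.13.2 to about one significant figure. I do not dispute the limits.

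**2. Inputs for the estimation check.**

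- Benefit limits from the stated p-values: z = 4.56, 3.29, 2.61, 2.33.
- Information fractions (assumption: proportional to median follow-up, final at 6 years): 2/6, 3/6, 4/6, 5/6, 1.
- Case (a), the two Mediterranean arms pooled against control at D.4's 11% risk: 2,333 × 0.11 + 4,666 × 0.0825 = 256.6 + 384.9 ≈ 642 events. With 2:1 allocation, information is 642 × 2/9 ≈ 142.6.
- Case (b), one arm against control at the observed 1.3% a year in D.4, with no allowance for ageing. Six years gives 7.55% compounded or 7.8% summed; 7.65% is used. Events are 2,333 × 0.0765 × 1.75 ≈ 312. With 1:1 allocation, information is 312/4 ≈ 78.1.

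Information is held fixed as the true HR varies, HR is taken as equal to RR, the harm limits are ignored, and the 10% losses in D.4 are not applied here (see step 5).

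**3. HR needed to stop at each look**, exp(−z/√(I·t)):

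| Case | 2 y | 3 y | 4 y | 5 y |
|---|---|---|---|---|
| (a) | 0.52 | 0.68 | 0.77 | 0.81 |
| (b) | 0.41 | 0.59 | 0.70 | 0.75 |

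Example, (a) at 2 years: 4.56/√(142.6 × 2/6) = 4.56/6.89 = 0.662, and exp(−0.662) = 0.52.

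**4. Simulated score process**, stopping at the first crossing. Means are of log HR, back-transformed; coverage is of the ordinary 95% interval.

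| True HR | Case | Early stop | Mean HR given a stop | Coverage given a stop | Mean HR, all trials | Coverage, all trials |
|---|---|---|---|---|---|---|
| 0.75 | (a) | 80% | 0.71 | 97% | 0.73 | 95% |
| 0.75 | (b) | 51% | 0.66 | 94% | 0.73 | 95% |
| 0.85 | (a) | 30% | 0.75 | 88% | 0.84 | 94% |
| 0.85 | (b) | 16% | 0.68 | 81% | 0.84 | 94% |

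**5. Sensitivity.** Applying the 10% losses to case (a) at true HR 0.75 gives a 75% chance of stopping and a mean HR of 0.70 given a stop. One arm at 11% risk with losses (about 404 events) gives 63% and 0.685.

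**6. What a bias adjustment would do.** Solving E(estimate | θ) = observed estimate (Whitehead) for a result exactly on a limit moves the HR by 0.011 to 0.019. At the 5-year limit it moves from 0.808 to 0.821 in (a) and from 0.749 to 0.766 in (b).

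**The case against.** The strongest case against the point has five parts.

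- **Silence is not a commitment.** D.12 does not say the HR will be left uncorrected after a stop, and such a rule is often placed in an analysis plan that is not shown. This stands as a limit on the wording: a reader might infer that the plan commits to an unadjusted figure, and the text does not support that. However, D.12 and D.13.2 already fix the test, the effect measure, the censoring and the stopping levels, so the rule belongs naturally beside them. If a separate plan already contains it, the point falls.
- **The average bias is small.** This is correct: 0.73 against 0.75, and 0.84 against 0.85. Trials that reach the final look err the other way (mean HR about 0.82-0.83 when the truth is 0.75). The larger figures apply only once a trial has stopped, which is the position of anyone reading a stopped trial.
- **Coverage is adequate at the design effect.** This is also correct: 97% and 94% given a stop at HR 0.75. Undercoverage appears when the true effect is weaker than planned.
- **The DSMB is not bound by the limits.** D.13.2 reserves stopping for a very large effect, so the stopping probabilities describe a mandatory rule and would be lower with restraint. Such restraint reduces how often the trial stops, but still selects large estimates.
- **The earlier trial is not comparable.** It had 58 events (44 + 14) and was faulted on several other grounds. Here the first look would have about 642/3 ≈ 214 events (a) or 312/3 ≈ 104 (b), and would stop in at most 0.5% of trials at HR 0.75. A reader might infer that this protocol repeats the fault it criticises. The documents support a parallel of kind, not of degree.

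**Conclusion.** The point holds as a gap in estimation and reporting. The plan offers four stops for benefit and specifies no estimate or interval that allows for them. Given an early stop, the ordinary HR would on average be about 0.04-0.09 too low if the truth is 0.75 (0.71 or 0.66), and about 0.10-0.17 too low if it is 0.85 (0.75 or 0.68).

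It would be wrong to conclude that the plan as a whole gives a materially biased result, that its intervals generally fail, or that its stopping limits are faulty. Across all outcomes the bias and the loss of coverage are slight, and the limits reproduce.

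The figures rest on information proportional to median follow-up, a stop at every crossing, and the two event scenarios above. This is a worthwhile, low-cost improvement, not a threat to the test of the primary hypothesis.

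**What to change.** Add a short paragraph to D.12 and D.13.2. If the trial stops at an interim look, the report gives, beside the ordinary HR, a bias-adjusted or median-unbiased HR with a confidence interval and p-value from stagewise ordering of the looks. It also states that the ordinary HR tends to overstate the benefit after an early stop. Which figure leads the conclusion is the authors' choice, provided both are shown.

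The cost is one paragraph and a few lines of code. Limits, sample size and conduct are unchanged. The adjusted HR will be slightly less favourable, by about 0.01-0.02. The adjustment corrects the average bias, and stagewise intervals hold their coverage over all trials. Neither removes all of the overstatement given a stop, which is why the explanatory sentence is needed as well.
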